**Discussion:**

One of the strengths of this study is that the feasibility for the BAAS clinical pathway was tested at first hand. Also, we will use validated questionnaires and functional tests to assess the patient’s recovery using robust outcomes. Moreover, the intervention was performed in two hospitals serving the targeted patient group and to reduce selection bias and improve generalizability. The limitations of this study protocol are that the lead author has an active role as a medical case manager (MCM) in one of the hospitals. Additionally, we will use the data from other prospective Dutch cohort studies to compare our findings regarding RTW to usual care. Since we will not perform an RCT, we will use propensity analysis to reduce the bias due to possible differences between these cohorts.

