**Table 1 Tab1:**
[figure not shown]
Measurements on different time points

T_0_ = baseline; T_1_ = 6 weeks after surgery; T_2_ = 3 months after surgery; T_3_ = 6 months after surgery; T_4_ = 9 months after surgery; T_5_ = 12 months after surgery

*Abbreviation*: *CSI* Central sensitization inventory, *DEMMI* De Morton mobility index, *FTST* Five time sit to stand test, *iPCQ*, *KOOS* Knee osteoarthritis outcome score, *WORQ* Work Osteoarthritis and joint-replacement questionnaire, *6 MWT* 6-Minute walk test, *30-STST* 30 Seconds sit to stand test. * = follow-up measurements stop after full return to work

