### Study intervention

The following BAAS work-directed care is offered to the patient, which was proven feasible (Additional file 1: Appendix I) [13]. The orthopedic surgeon provides information before surgery about returning to work after surgery in terms of expected time to RTW and the known prognostic factors like female gender, affirmative patient-reported work-relatedness of knee symptoms, high physical work demands, high Body Mass Index (BMI), and prolonged preoperative sick absence from work [39, 40]. Next, the orthopedic surgeon refers the patient to the MCM for a preoperative examination. During this preoperative examination, the patient fills out several questionnaires (WORQ, KOOS, CSI, WAS and iPCQ; Table 1) so the MCM gains insight in the preoperative status of the patient (Fig. 1). Then, the patient is subjected to performance-based physical tests to evaluate the functional capacity, namely a floor-to-waist lifting test and functionality tests, including the DEMMI, FTST, 30-STST, and 6MWT. During this preoperative examination, the patient is given information about the perioperative care and has the opportunity to ask questions about the recovery trajectory. The findings of the preoperative examination are used as baseline measurements for setting goals in the postoperative rehabilitation and as reference values for postoperative recovery. Next, the patient receives an accelerometer (PAM 2.0), including the option of feedback from the software application Atris (Peercode B.V.) during the preoperative examination. The movement data is accessible for the patient, the primary care physical therapist, and the MCM. A week later, the MCM calls the patient to discuss the current physical activity assessed by the accelerometer and give advice on the preferred physical preoperative preparation. For example, patients are advised to train functional movements required after surgery, such as walking with a walking aid, or are advised to maintain or increase the current physical fitness level by adhering to the WHO’s latest physical activity guideline [41]. The MCM then contacts the occupational physician to inform him or her about the participation of the patient in this clinical pathway. The patient is advised to consult the occupational physician before surgery. Then, the patient is referred to the occupational case manager (OCM; occupational assessor) by the MCM, to compile a report of beneficial and limiting factors regarding RTW after KA.

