### Statistical methods

#### Effectiveness

The effect of the BAAS care pathway on time to RTW will be statistically tested using survival analysis and gamma regression analysis including bootstrapping using R (version 4.1.0). Missing data will be handled by multivariate imputation using the aforementioned prognostic factors if possible [46]. For the repeated measurements on the time to RTW and/or full RTW, a mixed model will be used to test and estimate the size of the BAAS effect controlling for the following potential prognostic factors of delayed RTW, namely UKA vs TKA, primary vs revision KA, gender, BMI, physical nature of the job, preoperative sick leave, and patient-reported work-relatedness of knee symptoms. Hazard ratios including 95% confidence intervals will be calculated for the intervention group and tested against both control groups. In the absence of an empirically derived MCID, a difference of two weeks will be considered clinically relevant for first day of RTW and one week for full RTW. For interpreting the magnitude of the standard mean difference (SMD), three groups are defined: (i) small (SMD = 0 – 0.2); (ii) medium (SMD = 0.2 – 0.5) and (iii) large (SMD = 0.5–1.0) [47]. Sensitivity analyses on RTW will be performed for the two hospitals. Analyses will be conducted using both univariate and multivariate analyses to assess the effect size of the BAAS care pathway with and without controlling for variables. Lastly, because this control group is not from the same cohort as the intervention group, we will use propensity analysis (matched pairs) to correct for other confounding factors [48]. Potential prognostic factors for delayed RTW like UKA vs TKA gender, BMI, physical nature of the job, preoperative sick leave and patient-reported work-relatedness of knee symptoms will be used for patient matching. Secondary outcomes will be plotted in time and will be tested on differences between the usual care cohorts and the intervention cohort.

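### Secondary outcomes are to be tested between non-randomised cohorts with no stated use of their own preoperative score, so a preoperative gap could be reported as a BAAS effect

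*Protocol article*

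**What the plan says.** The analysis of secondary outcomes is one sentence at the end of Statistical methods, Effectiveness: "Secondary outcomes will be plotted in time and will be tested on differences between the usual care cohorts and the intervention cohort". It names no model, time point or covariate.

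The adjusted model earlier in that section is introduced for the primary outcomes: "For the repeated measurements on the time to RTW and/or full RTW, a mixed model will be used". For matching, the section lists "Potential prognostic factors for delayed RTW like UKA vs TKA gender, BMI, physical nature of the job, preoperative sick leave". The one other named factor is whether patients see their knee complaints as related to their work.

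The Abstract gives the reason for matching: "Since we will not perform an RCT, we will use propensity analysis to reduce the bias due to possible differences between these cohorts".

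Baseline scores exist. The footnote to Table 1 defines the schedule from T0 ("T_0_ = baseline; T_1_ = 6 weeks after surgery; T_2_ = 3 months after surgery; T_3_ = 6 months after surgery"), continuing to 12 months. Study intervention places WORQ, KOOS, CSI, WAS, iPCQ and the functional tests at the preoperative examination. The use it states for those results is clinical: "used as baseline measurements for setting goals in the postoperative rehabilitation and as reference values for postoperative recovery".

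**The concern.** In a randomised trial, leaving the baseline score out of the comparison costs mainly precision, because allocation makes the groups alike on average. Here the BAAS cohort comes from two hospitals and the comparators from other studies, so nothing makes preoperative knee function or work-related difficulty equal. A follow-up difference then mixes the starting gap with any effect of the pathway.

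The section is specific about confounding control, but the factors it names were chosen because they predict delayed RTW. For a score such as WORQ or KOOS, the obvious confounder is the same score before surgery, and that is not on the list. At stake is whether a reported advantage in function or symptoms reflects BAAS or only patients who started from a better position.

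**Working it through.** The protocol gives no T0 mean, SD, correlation or power for any secondary outcome, so there is no stated figure to reproduce. The numbers below are illustrative.

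**Inputs**
- From the protocol: significance level 0.05 (Sample size; taken as two-sided). The figure 125 also comes from Sample size, which does not say that it is per group.
- Assumed: n = 125 per group (75 as a smaller case); T0 gap g = 0.2 or 0.3 SD; T0-to-follow-up correlation r = 0.3, 0.5 or 0.7; no true effect; the same linear relation of follow-up to T0 in both cohorts; no reduction of the gap by matching or covariates.

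**Comparison of follow-up scores without T0**
- Spurious difference in SD units: b = r × g.
- Standard error: SE = √(2/n). For n = 125 this is √0.016 = 0.1265; for n = 75 it is 0.1633.
- Rejection rate: Φ(b/SE − 1.96) + Φ(−b/SE − 1.96).

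Worked case, n = 125, g = 0.2, r = 0.5: b = 0.10 and b/SE = 0.79. The rate is Φ(−1.17) + Φ(−2.75) = 0.121 + 0.003 = 0.124.

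| n per group | g (SD) | r = 0.3 | r = 0.5 | r = 0.7 |
|---|---|---|---|---|
| 125 | 0.2 | 7.6% | 12.4% | 19.8% |
| 125 | 0.3 | 11.0% | 22.0% | 38.2% |
| 75 | 0.2 | 6.6% | 9.4% | 13.8% |

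At g = 0.3 and r = 0.7 the spurious difference is 0.7 × 0.3 = 0.21 SD, just inside the band from 0.2 to 0.5 that the Effectiveness section calls medium. At g = 0.2 and r = 0.5 it is 0.10 SD, in the small band.

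**Alternatives, by simulation** (4,000 runs, n = 125 per group, same assumptions, T0 measured without error)
- Change from T0 does not cure the problem. Its expected spurious difference is (r − 1) × g, which has the opposite sign. At g = 0.3 the simulated rejection rate is 28.8%, 21.9% and 15.5% for r = 0.3, 0.5 and 0.7.
- Regression of follow-up on cohort and T0 keeps the rate between 4.6% and 5.3% for every non-zero gap tried (0.2, 0.3 and 0.5 SD).

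So it matters how T0 is used, not only that it is plotted.

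**The case against.** A reader might infer that the protocol has decided to run plain unadjusted tests and ignore T0. The text does not support that. It fixes no test, and plotting and testing over time is compatible with a longitudinal model that includes T0. This is a journal article, and model detail for a long list of secondary measures is often left to an analysis plan. Just before the sentence at issue, the same section plans analyses with and without controlling for variables and propensity matched pairs. The matching sentence is not expressly limited to RTW, and its factor list is introduced by *like*, so it is open. If matching covers secondary outcomes, BMI, job demands, sick leave and work-relatedness of symptoms could absorb part of a gap in WORQ or KOOS.

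That objection limits the point without removing it. The article commits to between-cohort tests and is detailed about covariates for RTW and costs, yet names no secondary outcome's own baseline anywhere. Matching on the named factors need not balance the score itself.

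Two further inferences should be resisted. First, T0 is not a clean pre-intervention value: Study intervention lists the surgeon's information on expected RTW, part of BAAS, before the examination at which T0 is measured. Second, a follow-up test of WAS cannot be assumed. The questionnaires named for postoperative evaluation are WORQ, KOOS and CSI, and the body of Table 1 is not visible.

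**Conclusion.** The point holds in a limited form. The protocol plans hypothesis tests of secondary outcomes between non-randomised cohorts, states no use of the outcome's T0 score in those tests, names only RTW prognostic factors for adjustment and matching, and leaves open whether the matched pairs apply. A preoperative gap could therefore be read as a BAAS effect; the protocol does not show that such a gap exists.

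The size is conditional: about 8% to 20% false positives for a 0.2 SD gap over correlations of 0.3 to 0.7, with 125 per group assumed and before any reduction from matching. The return to 5% after adjustment rests on a linear relation and an error-free T0. The primary aims, RTW and costs, are not affected, but the remedy is cheap and better than leaving the sentence as it stands.

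**What to change.** Replace the sentence on secondary outcomes with wording to this effect: each secondary outcome that has T0 and follow-up values in both BAAS and the comparison cohort will be compared by a longitudinal model of the follow-up scores on cohort, time and their interaction, adjusted for that outcome's own T0 score and the listed prognostic factors. Adding the T0 score to the propensity model would be an acceptable alternative. State whether the matched pairs are used for these outcomes. Where the comparison cohort has no T0 score, report the outcome descriptively and make no between-cohort test.

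The cost is a short passage of text and one covariate per model, using BAAS data already planned. Some between-cohort tests will be lost; how many is unknown, because the protocol does not say which comparison cohorts hold which T0 scores.

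T0 adjustment does not by itself deal with another selection. The Table 1 footnote says marked follow-up measurements end once a patient has fully returned to work, so later scores come increasingly from slower returners. The revised text should acknowledge this when it defines the time points compared.

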#### Economic evaluation

For the economic evaluation, missing data will be imputed using multivariate imputation using the aforementioned prognostic factors if possible [46]. An Ordinary Least Squares regression model with bootstrapping will be used to investigate the differences between the BAAS cohort and the usual care cohort of the ACTIVE trial. Lastly, because this control group is not from the same cohort as the intervention group, we will use propensity analysis to correct for the two different cohorts (intervention and control) [48]. Potential prognostic factors for delayed RTW like UKA vs TKA gender, BMI, physical nature of the job, preoperative sick leave, and patient-reported work-relatedness of knee symptoms will be used for patient matching. Results will be plotted for interpretation. The difference in costs and benefits are clinically relevant when the intervention has more financial benefit in comparison with usual care.

## Discussion

This study describes the protocol to evaluate the effectiveness of the BAAS care pathway for RTW as well as its costs and benefits. To the best of our knowledge, this is the first work-directed and patient-centered care after KA systematically involving health care experts other than an orthopedic surgeon and a physical therapist.

To the best of our knowledge, there is no previous study concerning minimal clinical differences in return to work after surgery. Therefore, we held a consensus meeting with authors [name] in which we concluded that a minimal clinical difference of two weeks on start to return to work and one week for full return to work is relevant.

Until now, no core outcome set exists for work participation including RTW to be used in intervention studies [49, 50]. Previous studies on RTW among patients with knee arthroplasty defined RTW in different ways. For example, Hylkema et al. measured the proportion of full RTW within 3, 6 or 12 months by asking the patient via a questionnaire whether they partially or fully returned to work, or not at all [6]. Tilbury et al. measured RTW by asking patients through a follow-up questionnaire what the duration from operation until the first day of RTW was [15]. Systematic reviews on RTW among patients with knee arthroplasty concluded that pooling data on RTW results in heterogeneity due to these varying RTW outcomes. To obtain a valid comparison, we used the same RTW definitions as those used in the prospective studies of Straat et al. and Zaanen et al. [17, 18]. While this RTW definition is needed to compare the results with the prospective studies, it also means that comparisons with other studies (vice versa) should be performed carefully.

The strengths of this protocol are that the BAAS clinical pathway was already proven feasible [13]. This way, not only did we learn that BAAS was feasible to implement, but we also learned important lessons to optimize the BAAS clinical pathway before evaluating its effectiveness, costs, and benefits. Also, the feasibility showed us promising results on the first day of RTW and full RTW in comparison to other Dutch prospective studies on RTW after KA. For example, patients started on average after 6.4 [6–8.1] weeks, in comparison to 12.9 weeks in the study of Tilbury et al. [15]. Patients fully returned to work on average after 12.4 [9.4–14.4] weeks, in comparison to the study of Hylkema et al., where 49% of the patients took more than six months to full RTW [6]. Of course, the present study should show whether these RTW data are reliable and valid. Also, we will use reliable and valid questionnaires and functional tests to assess the patient’s recovery. In addition, patients who experience widespread sensitization after KA are identified early and can be referred for multidisciplinary vocational rehabilitation [45, 51]. Also, by setting personal goals regarding work-related knee-straining activities using Goal Attainment Scaling, all the involved professionals have a focus towards work participation [52]. This probably supports both patient and professional in a timely and better collaboration between professionals within the medical and occupational trajectory. By focusing on these work-related activity goals, we aim to create more awareness in the multidisciplinary team about the values and needs of patients regarding their disability and what he or she is intended to achieve in work.

In transition processes, in which care as usual is replaced by a new care pathway, the essential role of the patients and health care professionals is often overlooked. Therefore, in our study the professionals involved in the care transitions in the two hospitals will collect and scrutinize the data together and, based on the results, determine what kind of action should be performed to enhance RTW in close contact with the patient. One of the consequences of this iterative cycle will be that all professionals as well as the patients involved become partners in achieving an optimal RTW. This way, the embedded scientist who, in daily practice, collects, creates, and reviews knowledge, and investigates the effectiveness of this newly implemented care pathway is an essential actor in creating and implementing future RTW pathways for other groups of working age patients.

Lastly, by using the data from two Dutch cohorts on RTW with similar inclusion criteria, our study is designed to be more cost-effective than a randomized controlled trial.

The limitations of this study protocol are that the lead author has an active role as an MCM in this study. This is why we included patients from a second hospital (ETZ). Also, we will not perform an RCT. We will use the data from two other prospective cohort studies with similar inclusion criteria to compare our findings to usual care. The care for knee arthroplasty is, fortunately, largely standardized in the Netherlands [44, 53]. Also, we will use propensity analysis to reduce the bias due to possible differences between our cohorts and the two comparison cohorts [17, 18].

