An interdisciplinary consultation is held the fourth or fifth week after surgery. The patient, the primary care physical therapist, the MCM, OCM, and occupational physician are invited to participate (Fig. 1). During this consultation, the progress, the attainment of the GAS goal, and RTW plan according to the Dutch Gatekeeper Improvement Act are discussed. If the patient has a job which he or she probably cannot return to, for example because of high knee demands due to prolonged kneeling and squatting, the possibility of work adaptions or even the topic of finding a less physically strenuous job are discussed (Fig. 1). The interdisciplinary consultation is continued if required, for instance based on unfavorable recovery data. If, after three months a delayed recovery is seen based on the patient’s experience and expert opinions of the MCM, OCM, and occupational physician, and supported by questionnaires, functional capacity evaluations and accelerometer data, the patient is referred to a multidisciplinary rehabilitation assessment (Fig. 1). Here, the patient is examined by a rehabilitation physician, occupational medicine specialist, physical therapist, and psychologist to assess barriers for delayed recovery and RTW, and whether the patient is eligible for an interdisciplinary vocational rehabilitation program. If so, the patient receives this interdisciplinary rehabilitation program [45].

The MCM from NS hospital, who is experienced in fulfilling the task of MCM through the previously performed feasibility study, will train two physical therapists working in ETZ. These physical therapists perform the tasks of an MCM in their hospital. Also, the MCMs of ETZ will be trained to perform all functional tests. Every two weeks a digital consultation will be held between all MCMs to discuss progress of the study and any questions that have arisen during the entire study period.

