### Data collection

For the effectiveness study, both date of surgery and RTW data are collected by the MCM. In addition to the RTW data, the preoperative data and health surveillance data (Fig. 1) are collected in the same file by the same MCM.

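### The second hospital limits the lead author's direct role but does not separate care from outcome recording: at both sites the medical case manager who coaches the patient also collects the return-to-work dates

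*Protocol article*

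**What the plan says.** The limitation and its remedy stand together in the Discussion: "The limitations of this study protocol are that the lead author has an active role as an MCM in this study", followed by "This is why we included patients from a second hospital (ETZ". The abstract narrows the role to one site: "the lead author has an active role as a medical case manager (MCM) in one of the hospitals".

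On who measures the primary outcome, Data collection says that "both date of surgery and RTW data are collected by the MCM". It makes no distinction by site and adds that the same MCM keeps the preoperative and surveillance data in the same file.

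On ETZ, Study intervention says that the MCM from NS trains two physical therapists there, and that "These physical therapists perform the tasks of an MCM in their hospital". It continues: "Every two weeks a digital consultation will be held between all MCMs to discuss progress of the study".

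The only analysis that separates the sites is in Statistical methods, Effectiveness: "Sensitivity analyses on RTW will be performed for the two hospitals".

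**The concern.** Two problems lie close together here. One is that an author of the study treats some of its patients. The other is that whoever delivers the pathway also collects the date on which the pathway is judged. A second hospital can dilute the first, because other people treat those patients. It leaves the second as it was, because the ETZ case managers hold the same double task.

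This matters more than it would in a trial with a concurrent control group measured in the same way. The comparators are two external cohorts that had no BAAS case manager. A systematic error in dating RTW among BAAS patients, relative to how those cohorts dated it, becomes part of the estimated effect. Propensity matching balances patient characteristics, not the way the date was obtained. A reader told that the second hospital deals with the conflict could take similar results at the two hospitals as evidence of sound outcome recording, which this design cannot supply.

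**Working it through.** **Who does what, by site**

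| Task | NS | ETZ | Source |
|---|---|---|---|
| Testing, coaching, work goal, weekly accelerometer review, RTW consultation | MCM | MCM | Study intervention |
| Collecting surgery and RTW dates | MCM | MCM | Data collection |
| Training | Experienced from the feasibility study | Trained by the MCM from NS | Study intervention |
| Two-weekly contact | All MCMs | All MCMs | Study intervention |
| Lead author as MCM | Yes (inferred) | No (inferred) | Abstract, Study intervention, Discussion |

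The last row is an inference: the article says one hospital and does not name it. It is the only row in which the sites differ in a way that bears on the conflict of interest.

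**What the analysis by hospital can show**

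Let *b* be the mean dating error at a site, relative to the dating in the usual-care cohort. On the scale of mean days:

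- Shift in the pooled estimate = (75 × *b*_NS + 75 × *b*_ETZ) / 150
- Shift in the contrast between hospitals = *b*_NS − *b*_ETZ

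Two cases, each with an assumed error of 4 days:

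- Error at NS only: pooled shift = (75 × 4 + 75 × 0)/150 = 2 days; contrast = 4 days. Adding ETZ halves the bias and makes it visible in principle.
- The same error at both sites: pooled shift = (75 × 4 + 75 × 4)/150 = 4 days; contrast = 0 days. ETZ neither dilutes the bias nor reveals it.

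**Size against the plan's own thresholds**

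The thresholds are two weeks (14 days) for first RTW and one week (7 days) for full RTW (Statistical methods, Effectiveness). The shifts are assumptions.

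| Assumed mean shift | First RTW | Full RTW |
|---|---|---|
| 2 days | 2/14 = 14% | 2/7 = 29% |
| 4 days | 4/14 = 29% | 4/7 = 57% |
| 7 days | 7/14 = 50% | 7/7 = 100% |

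**Side check: an error at one site only**

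The article gives no standard deviation, so I backed one out of the sample-size section (125 patients, two-week difference, power 0.8, alpha 0.05). I assumed a two-sided comparison of two means.

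SD = 2 / [(1.96 + 0.84) × √(2/n)]

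- 125 read as the total, n = 62.5 per group: SD about 4.0 weeks
- 125 read as per group, n = 125: SD about 5.6 weeks

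The difference between hospitals detectable with 80% power is (1.96 + 0.84) × SD × √(2/m), with *m* patients per hospital:

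- m = 75: 1.8 to 2.6 weeks
- m = 60 (after 20% loss): 2.0 to 2.9 weeks

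Power to see a one-week difference between hospitals is 16% to 34% over these four cases. For a two-week difference it is 49% to 87%. Even an error confined to one hospital could therefore be missed.

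**The case against.** The strongest reply is that the Discussion offers ETZ for one stated limitation, the lead author's own role, and for that it does something real: half the patients are treated by others. Nothing says that the ETZ case managers are authors. This stands, and it rules out the reading that the safeguard fails altogether.

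Several other stronger readings are tempting and are not supported.

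- **That the case manager is free to choose the date.** Primary outcomes treats RTW as self-reported and ties full RTW for employees to contract hours. Both limit discretion, though neither takes collection out of the MCM's hands.
- **That prompting an early return is bias.** A real earlier return is what the pathway is meant to achieve. Only mis-dating is bias.
- **That mis-dating must favour BAAS.** The direction depends partly on how the usual-care cohorts recorded their dates, which the article does not show.
- **That the teams steer by pooled RTW results.** The Discussion says professionals of both hospitals will review data together and "determine what kind of action should be performed to enhance RTW in close contact with the patient". That fits decisions about individual patients, and no text describes pooled review.
- **That the plan will count agreement between hospitals as reassurance.** It announces the analysis and gives no rule for reading it.

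It is also fair to say that a condensed article may leave verification of dates to the full protocol. The point made here is narrower. The article itself offers ETZ as the answer, and itself assigns outcome collection to the MCM without distinction by site.

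**Conclusion.** The point holds in a limited form. ETZ removes the lead author's hands-on role for 75 of 150 patients, but the union of care delivery and outcome recording is the same for all 150. The analysis by hospital tests site differences. It cannot detect a dating error shared by both sites, and such an error would enter the comparison with the external cohorts in full.

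Neither the size nor the direction of any error is known. The percentages above show only what assumed shifts would amount to. They apply to mean days and do not translate directly into hazard ratios. The conclusion rests on reading Data collection as applying to both hospitals, which its wording supports. It does not depend on which hospital the lead author works in.

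**What to change.** 1. Keep the MCM log as the primary source of RTW dates.
2. Add two patient-reported items, date of first RTW and date of full RTW, to the cost questionnaire already planned at 3, 6, 9 and 12 months.
3. Make sure these items also reach each patient once after full RTW. Table 1 marks some measurements as ending at full RTW, and the marked rows are not visible in the text available. If the questionnaire is among them, a patient who returns between time points would never report the date.
4. Report agreement between log and patient report by hospital, as the mean difference in days with its spread. Repeat the primary RTW comparison with the patient-reported dates as a sensitivity analysis.
5. In the Discussion, replace the claim for ETZ. Say that the second hospital limits the lead author's direct role, and that the hospital split tests site differences only, not bias from case managers recording the outcome.

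The cost is two questionnaire items, one further request after full RTW, one agreement table, one sensitivity analysis and a few sentences. No extra staff are needed.

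There are drawbacks. Recalled dates are less exact than a running log, which is why the log stays primary. Surgery was scheduled from January 2022, so patients already past follow-up can be asked only in retrospect. Patient report reduces the case manager's influence on the date but does not remove it.
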